### Assessments for efficacy

At discharge (visit 3), and at follow-up evaluations (visits 4, 5, and 6), the patient will be evaluated for post-surgical complications (such as hematoma/seroma, wound infection, reinterventions). Complications will be evaluated by the surgeon during surgery and at discharge. Any complications will be recorded in the CRF. If the complication leads to additional surgical interventions, it needs to be noted in the CRF. The need for blood transfusions will be noted in the CRF.

### Follow-up of adverse events

During and following a subject’s participation in a clinical trial, the investigator/institution should ensure that adequate medical care is provided to the subject for any adverse events, including clinically significant laboratory values related to the trial. The investigator/institution should inform the subject when medical care is needed for adverse event(s) of which the investigator becomes aware. The follow-up information should only include new (updated and/or additional) information that reflects the situation at the time of the investigator’s signature. All non-serious AEs classified as severe or possibly/probably related to the trial product must be followed until the subject has recovered and all queries have been resolved. However, cases of chronic conditions can be closed with an outcome of “recovering” or “not recovered.” If subjects die from another event, these cases can be closed with an outcome of “recovering” or “not recovered.” The investigator must ensure that the worst case severity and seriousness is kept consistent through the series of adverse event form and related adverse event follow-up form(s). The investigator must forward follow-up information on non-serious AEs on the adverse event follow-up form. All serious AEs must be followed until the outcome of the event is recovered, recovered with sequelae, or fatal and until all queries have been resolved. For cases of chronic conditions and cancer or if the subject dies from another event, follow-up until the outcome categories are “recovered,” “recovered with sequelae,” or “fatal” is not required, as these cases can be closed with an outcome of “recovering” or “not recovered.” There are some adverse events that are expected for the population of the study like allergic reaction to the mesh, infection of the mesh, and migration of the mesh.

### Sample size

No previous data exist on the efficacy of swine dermal collagen prosthesis in preventing incisional hernia in peritonitis patients. The following published data will be used in our sample size calculation:
“The risk of incisional hernia in patients with peritonitis is elevated, with an incidence of up to 54%, compared with an incidence of 11–26% in general surgical population” [1–3, 20].“The result of this pooled analysis suggests a benefit to prophylactic mesh placement during laparotomy closure in high-risk patients with a significantly reduced incidence of incisional hernia without any significant differences in seroma formation and wound infection rate” [19].“The use of biologic mesh for ventral hernia repair results in less infectious wound complications but similar recurrence rate compared with non-biologic mesh” [18].

The sample size has been calculated using statpages.org (proportion difference power/sample size calculation). The sample size was defined in 90 patients (45 in each arm).

### Statistical analysis

Only the data of participants who complete the follow-up will be considered. Descriptive analysis will be performed for all pre-operative, operative, and follow-up information. For categorical variables, we will use chi-square test, for non-categorical one the *t*-test. The primary endpoint, % of patients presenting incisional hernia at 3, 6, and 12 months, will be analyzed between treatment groups using a logistic regression model, presenting odds ratio comparisons of the two. Surgery time, time to drain removal and length of stay in hospital will be analyzed between treatment groups using Student’s *T* test if data are normally distributed and with Mann-Whitney test if data are not normally distributed. The distribution of data will be evaluated with the Shapiro-Francia test. The number of patients who died will be analyzed between treatment groups using a chi-square test.

All statistical comparisons will be based on two sided tests with a 5% significance level.

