## Methods/design

### Objective

The primary objective is:

1) Evaluate the possibility to reduce the incisional hernia rate (from 50% to 20%) in patients undergoing urgent/emergent laparotomy in contaminated/infected field with peritonitis by using swine dermal collagen prosthesis preperitoneal positioning as a prophylactic procedure.

The secondary objective is:

1) Evaluate the impact on morbidity and mortality of the systematic swine dermal collagen prosthesis preperitoneal positioning as a prophylaxis for incisional hernia in patients operated in contaminated/infected field with peritonitis.

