### Study endpoint

The primary endpoint is to evaluate the incisional hernia rate at 3, 6, and 12 months after surgery in each group (study arm and control arm). The secondaries endpoints are to define morbidity (adverse events (AE) and serious adverse events (SAE)), surgery time, time to drain removal, length of stay in hospital, and mortality.

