#### Informed consent

All the criteria must be satisfied for included the patient in the study.

The exclusion criteria are:
Patients aged < 18 years oldInformed consent refusalNo clinical and/or laboratory and/or radiological evidence/signs of peritonitis of any originSurgical indication for laparotomies other than midline onePregnancy

The presence of even one of these exclusion criteria does not allow the patient to participate at the study.

The subject may withdraw at will at any time. The patient may be withdrawn from the trial at the discretion of the investigator for safety concerns. If the patient withdraws or is withdrawn at any time after receiving trial product, final safety information will be obtained. Patients who are deemed during surgery not suitable included in this protocol will be withdrawn from the study. In case a subject is being prematurely withdrawn from the trial, the investigator will ensure that the procedures for the last visit are undertaken, if possible. The primary reason (adverse event, non- compliance with protocol or other) for discontinuation must be specified in the CRF. A patient withdrawn from the study will be analyzed according to evaluability of subjects for analysis.

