### Visit procedures

The randomization and the study data are collected using an online form (https://prophybiom.easycrf.cloud). The access at this form is allowed only at the participant at the study that has a username and password. Investigators who conduct follow-up assessments will not be blinded.

The study comprises of the following visits (Table 1):

**Table 1 Tab1:** Time and event chart

Nomenclature	Visit 1	Visit 2	Visit 3	Visits 4, 5, and 6
	Screening	Treatment	Discharge	Follow-up
	Screening, baseline	Surgery	Discharge	Follow-up
**Informed consent**	**√**			
**Inclusion/exclusion criteria**	**√**			
**Demographic data (sex, age, weight, height, BMI)**	**√**			
**Medical history/concomitant illness**	**√**			
**Physical examination**	**√**		**√**	**√**
**ASA classification**	**√**			
**Vital signs**	**√**	**√**		
**Body weight and height**	**√**			
**ECG (12 lead)**	**√**			
**Hematology and coagulation parameters**	**√**		**√**	
**Blood chemistry**	**√**		**√**	
**Antibiotic therapy**	**√**			
**Start of LMW heparin**	**√**			
**Concomitant medication**^**a**^	**√ continuously**			
**Start and end of surgery**		**√**		
**Site and length of incision**		**√**		
**Peritonitis grade assessment**		**√**		
**Peritoneal fluid sampling for microbiological examination**		**√**		
**Contamination assessment**		**√**		
**Intestinal resection**		**√**		
**Stoma creation**		**√**		
**Surgical complications**		**√**		
**Surgical drain placement**		**√**		
**Surgery report**		**√**		
**Time of drain removal**			**√**	
**Length of stay in hospital**			**√**	
**Post-surgical complications**			**√**	**√**
**Abdominal wall ultrasound**				**√**
**Adverse events**	**√ continuously**			

^a^This includes use of any blood transfusions that should be inserted in the CRF as type (red blood cells. FFP, platelets)

• Visit 1: Screening and baseline visit: screening of patient, baseline examination, pre-surgery assessment, informed consent

• Visit 2: Treatment visit: surgery

• Visit 3: Discharge from hospital: recording of post-surgical complications

• Visits 4, 5, and 6: Post surgery follow-up visits: at 3, 6, and 12 months post-surgery. All patients will perform an abdominal wall ultrasound to document the presence or not of incisional hernia. At the last visit, the data collected is the same of the other visits. The patients are called 15 days prior to the follow-up visit to remind them of the appointment.

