## Discussion

To date, no randomized clinical trials have examined the efficacy of biological mesh in contaminated field, and no previous data exist on the efficacy of swine dermal collagen prosthesis in preventing incisional hernia in peritonitis patients.

Our randomized controlled trials have the aim to evaluate the impact of biological prosthesis in contaminated field, reduce the incidence of incisional hernia from 20 to 50%, and determine the impact on morbidity and mortality of the systematic swine dermal collagen prosthesis preperitoneal positioning.

The result of our study will increase the knowledge about swine dermal collagen prosthesis in peritonitis patients. The long follow-up of over 36 months would permit to understand the rate of incisional hernia in the medium-long term by comparing the patients treated with the biological prosthesis and those on which traditional treatment was performed. If the use of the swine biological prosthesis will prove to be an advantage (or disadvantage) in terms of reducing early and late post-operative complications (wound infections, seroma, wound dehiscence, bleeding, incisional hernia, re-surgery), it will probably be possible to draw up more precise guidelines in case of median laparotomies during surgery for peritonitis. In fact, the absence of clear indications on the approach in case of laparotomies on infected fields leads the surgeon to have random and different behaviors from case to case without determine the cause of possible post-operative complications.

Moreover, surgery performed in urgency for peritonitis is accompanied by a percentage of complications that are certainly higher than elective surgery. Trying to understand if it is possible to reduce the percentage of complications due to incisional hernias could also help to reduce the direct and indirect costs associated with surgery. Thus, studies that are aimed to determinate if it is possible are needed. The results of this trial will support a tangible decision-making process for choosing appropriate technical approach in abdominal parietal synthesis in peritonitis.

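### Restricting every analysis to patients who complete follow-up removes all deaths up to 12 months from the planned mortality test and discards other outcomes already observed

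*Protocol article*

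**What the plan says.** The Statistical analysis section of the protocol article opens with the analysis population: "Only the data of participants who complete the follow-up will be considered". No endpoint is excepted. The analyses that follow in that section are:

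- Incisional hernia at 3, 6 and 12 months, the primary endpoint, "will be analyzed between treatment groups using a logistic regression model, presenting odds ratio comparisons of the two".
- Student's t or Mann-Whitney test for length of stay, drain removal time and duration of surgery.
- Deaths: "The number of patients who died will be analyzed between treatment groups using a chi-square test".

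The only secondary objective is stated as: "Evaluate the impact on morbidity and mortality of the systematic swine dermal collagen prosthesis preperitoneal positioning". Study endpoint lists adverse and serious adverse events together with "surgery time, time to drain removal, length of stay in hospital, and mortality".

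Visit procedures sets the schedule: "Post surgery follow-up visits: at 3, 6, and 12 months post-surgery". The Discussion mentions a longer period ("The long follow-up of over 36 months would permit to understand the rate of incisional hernia"), but no visit after month 12 is scheduled.

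The only other sentence on who is analysed is in the Informed consent section: "A patient withdrawn from the study will be analyzed according to evaluability of subjects for analysis". The article does not define evaluability, and that sentence does not mention deaths.

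**The concern.** The population rule and the mortality test cannot both be applied as written. A patient who dies before month 12 does not complete a 12-month follow-up, so the rule removes exactly the patients the test is meant to count. These are emergency patients with peritonitis, and mortality is half of the stated secondary objective.

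The effect goes beyond deaths. A patient who withdraws or is lost after discharge also leaves every table, although the operative and in-hospital outcomes have already been recorded. A hernia documented by ultrasound at month 3 or 6 is discarded if the patient does not reach month 12, although the Background says most incisional hernias develop in the first 3 months.

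Completion is also known only after randomisation and may be affected by allocation. Comparing arms among completers gives up the protection of randomisation for the primary endpoint.

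**Working it through.** **1. Mortality under the rule.** Let d1 and d2 be the deaths before month 12 in the two arms of 45. The completer set contains at most 45 − d1 and 45 − d2 patients, none of whom died in that period. The table is therefore 0/(45 − d1) versus 0/(45 − d2) for any d1 and d2. The expected number of deaths in each arm is n × 0/(n1 + n2) = 0. The chi-square statistic divides by the expected counts, so it is undefined.

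Illustration with assumed deaths of 4/45 versus 13/45:

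- All randomised, no continuity correction: χ² = 90 × (4 × 32 − 13 × 41)² / (45 × 45 × 17 × 73) = 90 × 405² / 2,513,025 = 5.87, p = 0.015.
- Completers: 0/41 versus 0/32. No test is possible.

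**2. Observed data that the rule discards** (timing from Table 1 of the article).

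| Outcome | When recorded | Lost if the patient later dies, withdraws or misses month 12? |
|---|---|---|
| Surgery time | Visit 2 (surgery) | Yes |
| Drain removal, length of stay | Visit 3 (discharge) | Yes |
| Adverse events, including fatal ones | Continuously | Yes |
| Hernia on ultrasound at 3 or 6 months | Visits 4 and 5 | Yes |

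**3. The planned sample size.** The article states 90 patients (45 per arm), a reduction in hernia from 50% to 20%, and a two-sided 5% level. It states no power; 80% is assumed here.

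- n = [1.96 × √(2 × 0.35 × 0.65) + 0.8416 × √(0.25 + 0.16)]² / 0.30² = (1.322 + 0.539)² / 0.09 = 38.5 per arm.
- With continuity correction: (38.5/4) × [1 + √(1 + 4/(38.5 × 0.30))]² = 44.9, so 45 per arm and 90 in total.

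The stated 90 is reproduced exactly, and this calculation leaves no allowance for death or loss.

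**4. Size of the loss.** The article gives no death or loss rate, so the rates below are assumptions. Power is for 50% versus 20% without continuity correction: Φ{[0.30 × √n − 1.322] / 0.640}.

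| Assumed non-completion | Removed of 90 | Remaining | n per arm (rounded down) | Power |
|---|---|---|---|---|
| 0% | 0 | 90 | 45 | 86.0% |
| 10% | 9 | 81 | 40 | 81.6% |
| 20% | 18 | 72 | 36 | 77.2% |
| 30% | 27 | 63 | 31 | 70.7% |

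The power column shows the cost of dropping these patients from the hernia analysis. An all-randomised analysis recovers hernias already documented, but it cannot recover an outcome that was never observed.

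**The case against.** **The authors evidently meant to count deaths.** They plan a test on them, Follow-up of adverse events tracks serious events to outcomes that include a fatal one, and Visit procedures requires an End of Trial Form even from patients who cannot attend. Completion is not defined, and follow-up until death might be regarded as complete. This stands as a reading of intent: a reader should not infer that a 0-versus-0 test was deliberately planned. But the text does not say that death counts as completion. Even if it did, withdrawn and lost patients would still be dropped. The longer follow-up in the Discussion does not help, since a longer period excludes more deaths.

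**The Informed consent section may look like a contradiction.** A reader might infer that its evaluability sentence conflicts with the completer rule. That is not established, because completing follow-up could be the evaluability criterion. The term is undefined in the article and may be defined in a document not shown.

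**Bias in the primary comparison is not demonstrated.** Nothing in the article shows that non-completion differs by arm. Mesh complications matter here only if they lead to withdrawal, loss or death. What stands is a risk of unknown size and direction.

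**Analysis detail belongs in an SAP.** This is fair for the handling of missing hernia status. It does not excuse the population rule, which the article itself fixes and which is incompatible with its own mortality test.

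**Conclusion.** The point holds as a fault in what the article states. Applied as written, the rule leaves no deaths up to 12 months in either arm, so the mortality part of the secondary objective cannot be answered and the morbidity part loses its fatal events. It also discards operative, in-hospital and early hernia data that were observed, and it makes the primary comparison conditional on a post-randomisation event.

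The mortality result is purely logical and rests on one reading: that completing follow-up means reaching the 12-month visit, the last one scheduled. The figures of 9, 18 or 27 patients removed, and the matching power, rest on assumed non-completion of 10%, 20% or 30% and are not estimates for this trial.

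The documents do not support a claim that the hernia result will be biased in a particular direction. Nor do they show that one particular method, such as a competing-risk analysis, is required.

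**What to change.** 1. Replace the opening sentence of Statistical analysis with a statement that all randomised patients are analysed in the arm allocated.
2. Count every death. Use all randomised patients for mortality, adverse and serious adverse events, and the operative and in-hospital outcomes.
3. For hernia, count any hernia documented up to the last available assessment, and state in advance how death and missing visits are handled. A competing-event analysis or multiple imputation are options; either would change or supplement the stated logistic regression, so the choice should be made explicitly.
4. Keep the completer analysis as a sensitivity analysis only.
5. Define evaluability in the Informed consent section consistently with this. Cover patients judged unsuitable during surgery: they have already been randomised, since Patients recruitment places randomisation before the laparotomy.

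The cost is rewording and modest extra analysis. It should not be assumed that no further data are needed: Table 1 has no row for vital status, the content of the End of Trial Form is not described, and last-visit procedures after withdrawal are done only where possible. The sponsor should confirm that the form records vital status and date of death. Study design reports six patients enrolled at the time of writing, so at that stage the rule could be changed before most outcomes had accrued.

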## Introduction

### Background and rationale

Patients undergoing emergency surgery for peritonitis are at increased risk of abdominal wall-related complications. In patients with peritonitis, the risk of incisional hernia (IH) is extremely elevated. The incidence of IH in patients operated with peritonitis is up to 54%, compared with an incidence of 11–26% in the general surgical population [1–3]. Moreover, up to 24.1% of patients with peritonitis undergoing emergency laparotomy may develop fascial dehiscence [4]. The evaluation of quality of life of patients with IH showed lower mean scores on physical components of health-related quality of life and body image [5]. The prophylactic mesh implantation demonstrated to reduce the incisional hernia rate in patients undergoing vascular or bariatric procedures [6–8]. However, the intraperitoneal non absorbable mesh implantation in infected fields is generally considered at least of doubtful safety because of the theoretical increased risk of chronic mesh infection and enterocutaneous fistula [9–11]. Most incisional hernias develop during the first 3 months after surgery, which represents the critical period for the healing of transected muscular and fibrous layers of the abdominal wall [12]. However, most studies recommended a long-term follow-up period of up to at least 5 years for midline abdominal incisions to determine the real incisional hernia rate [13, 14]. The midline abdominal incision is preferred in abdominal surgery, as it provides wide and rapid access compared other incisions. However, the incidence of incisional hernias is higher following midline abdominal incisions than in other abdominal incisions [15]. In emergency surgery, the midline incision in the majority of cases is a necessity. Several factors affect the process of wound healing: surgical site infection, poor surgical technique, and patient-related factors (i.e., peritonitis, old age, obesity, diabetes mellitus, nutritional deficiencies, hepatic cirrhosis, jaundice, renal impairment, malignancy, cardiac disease, chest problems, previous abdominal incisions, steroid therapy). Data about the use of biological prosthesis in infected fields are scarce and derive principally from case reports and case series [16]. However, indications about their use and usefulness in infected fields have been recently published by the Italian Biological Prosthesis Working Group (IBPWG) [16]. A previously published prospective observational study evaluated the efficacy of implantation of biological prosthesis in high risk patients in order to reduce the incidence of incisional hernia. This study suggested the efficacy of this kind of prosthesis in reducing incisional hernia rate in patients with multiple risk factors [17]. A recently published meta-analysis showed as the use of biological prosthesis in ventral hernia repair resulted in a lower infectious wound complication rate but in an similar recurrence rate. These results support the application of biological prosthesis in high risk patients [18]. One recent systematic review evaluated the positive effect on incisional hernia rate of the prophylactic mesh positioning in high risk patients [19]. No randomized trials have been published since now about the use of biological prosthesis in contaminated or infected fields. The primary endpoint is to evaluate the incisional hernia rate after laparotomy at 3–6–12 months in patients with or without the mesh. So, the rationale of the trial is to evaluate the efficacy of the use of swine dermal collagen prosthesis implanted preperitoneally as a prophylactic procedure against incisional hernia in patients operated in urgency/emergency setting in contaminated/infected fields with peritonitis. The aim of the study is to reduce the incidence of incisional hernia from 50% to 20%.

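### The primary endpoint names three visits and no decisive one, each comparison at 5%, and does not say whether hernia is counted cumulatively or at the visit

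*Protocol article*

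**What the plan says.** The protocol article defines the primary endpoint under Study endpoint: "The primary endpoint is to evaluate the incisional hernia rate at 3, 6, and 12 months after surgery in each group". The Statistical analysis section repeats it as a percentage of patients: "The primary endpoint, % of patients presenting incisional hernia at 3, 6, and 12 months, will be analyzed between treatment groups". The method given there is "using a logistic regression model, presenting odds ratio comparisons of the two". The same section fixes the level: "All statistical comparisons will be based on two sided tests with a 5% significance level". No section singles out a visit, orders the three, or adjusts for them.

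The target is a single pair of rates. Background and rationale says: "The aim of the study is to reduce the incidence of incisional hernia from 50% to 20" per cent. The Objective repeats the pair, and neither section ties it to a visit. Sample size gives 90 patients, 45 per arm, from an online calculator for a difference in proportions.

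On counting, Visit procedures has ultrasound at 3, 6 and 12 months to record whether a hernia is present. Assessments for efficacy records reinterventions as post-surgical complications. The Discussion lists dehiscence and repeat surgery as items apart from incisional hernia.

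**The concern.** Three readings share the title of primary endpoint and each carries the full 5%. If the visits disagree, the protocol does not say which one decides the trial. A report could then rest on whichever visit is significant, and the primary false-positive rate would exceed the stated level. The 50% to 20% target would also lack a time to which it applies.

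The second gap is the counting rule. The Background speaks of *incidence*, which suggests counting each patient once a hernia has occurred. The Statistical analysis speaks of patients *presenting* hernia at a visit, which suggests status on the day. The two differ for a patient whose hernia is found and repaired between visits: a case under the first rule, possibly hernia-free under the second. Two analysts following this text could obtain different 12-month rates from the same data.

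**Working it through.** **1. The plan's own figure.** Inputs: 50% and 20% (Background, Objective); two-sided 5% (Statistical analysis); 1:1 allocation (Patients recruitment). Power is not stated, so 80% is assumed.

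Without continuity correction, n₀ = [z(α/2)·√(2p̄q̄) + z(β)·√(p₁q₁ + p₂q₂)]² / d², with p̄ = 0.35 and d = 0.30:

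n₀ = [1.960 × √0.455 + 0.842 × √0.41]² / 0.09 = (1.322 + 0.539)² / 0.09 = 38.5, so 39 per arm (78 in total).

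With continuity correction, n = (n₀/4)·[1 + √(1 + 4/(n₀d))]² = 9.62 × (1 + 1.160)² = 44.9, so 45 per arm. This matches the stated 90 exactly. Uncorrected at 85% power the result is 44 per arm (88), which is close. Either way, the calculation is for one comparison at one full 5%.

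**2. Upper reference for three tests.** If the three tests were independent: 1 − 0.95³ = 14.3%.

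**3. Allowing for correlation.** The same patients are read three times. With cumulative status and rates p < q at two visits, the correlation is √[p(1−q) / (q(1−p))]. For 30/40/50% at 3/6/12 months the correlations are 0.80 (3 and 6), 0.65 (3 and 12) and 0.82 (6 and 12).

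The table gives the chance that at least one of three two-sided 5% tests is significant with no true effect. The simulations use 45 per arm and 300,000 trials per pattern. The article does not give the onset split, so the patterns are assumptions.

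| Assumed hernia at 3/6/12 months | Share by 3 months | Normal approximation | Simulated, Wald | Simulated, chi-square |
|---|---|---|---|---|
| 45/48/50% | 90% | 7.6% | 6.7% | 6.9% |
| 40/45/50% | 80% | 8.7% | 7.7% | 8.1% |
| 30/40/50% | 60% | 10.1% | 9.5% | 10.0% |
| 20/28/35% | 57% | 9.9% | 9.4% | 10.6% |
| 26/40/50% | 52% | 10.6% | 9.7% | 10.5% |
| 15/30/50% | 30% | 11.8% | 10.3% | 12.0% |
| 10/25/50% | 20% | 12.4% | 9.3% | 13.1% |

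The Background says that most incisional hernias develop in the first 3 months. The first five rows fit that: about 7% to 10%, the highest single value being 10.6%. The last two rows do not fit it.

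**4. Cost of keeping three routes to success.** With Bonferroni, each test is at 0.05/3 = 0.0167, and z rises from 1.960 to 2.394:

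n₀ = (2.394 × 0.6745 + 0.539)² / 0.09 = 51.5, so 52 per arm (104). With continuity correction it is 59 per arm (118).

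At 45 per arm, power without continuity correction is Φ[(0.30·√45 − z·√0.455)/√0.41]. This falls from Φ(1.08) = 86% at 5% to Φ(0.62) = 73% at 0.0167.

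**The case against.** The protocol speaks of one logistic regression model, does not say in so many words that three separate tests will be run, and nowhere says that one significant visit is enough. This stands: the inflation is conditional on that reading. It does not rescue the text, because no time term, repeated-measures structure or cumulative outcome is given. If one model is meant, the article does not say for which outcome.

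A statistical analysis plan not seen here may name the visit. But the protocol itself fixes both the endpoint and the level, and the decisive time point belongs with them.

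The simulation uses cumulative status without repairs, although the endpoint might be status at the visit. That is fair. Repairs between visits would be expected to loosen the correlation, and so move the error towards the independent reference rather than below the figures given.

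A reader might go further in three ways that the document does not support:

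- *A repaired wall failure counts as hernia-free.* No section says so. It is one possible result of the word *presenting*, and *incidence* and *rate* elsewhere point the other way.
- *About a quarter of patients would be misclassified.* The Background does say that "up to 24.1% of patients with peritonitis undergoing emergency laparotomy may develop fascial dehiscence". That is an upper figure for dehiscence. It is not a rate of dehiscence re-closed and hernia-free at 12 months, nor a rate of hernia repair, so it does not measure this problem.
- *The error is 13%.* That value needs only a fifth of hernias to appear by 3 months, contrary to the Background, and the chi-square test; the Wald test gives 9.3% for the same pattern.

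**Conclusion.** The point holds in limited form. The primary endpoint has three visits, no decisive one and no multiplicity rule, with 5% for every comparison, while the sample size fits a single comparison. If any one visit can support the claim, the false-positive chance is about 7% to 10%, or 1.4 to 2 times the stated 5%. This assumes that most hernias arise by 3 months, that status is cumulative and that there are 45 per arm. Later onset raises it to about 10% (Wald) or 13% (chi-square).

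Separately, cumulative and at-visit counting are not distinguished, so a hernia repaired before a visit could be scored as hernia-free. The documents give no figure for how often that would happen. Both gaps concern the definition of the primary result and should be closed before any comparison between arms.

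**What to change.** Name one primary endpoint: cumulative incidence of incisional hernia by 12 months. Count a patient as an event at the first documentation by examination or ultrasound at any visit, or at any incisional hernia repair since randomisation. Make one logistic regression comparison at two-sided 5%, and state that the 50% to 20% target refers to this endpoint. Report the 3- and 6-month rates as secondary and descriptive.

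Report fascial dehiscence separately, or in a sensitivity analysis that counts it as an event. Building it into the primary endpoint would create a composite for which the 50% to 20% target was not set, so the event rates and the sample size would need rechecking.

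The cost is a protocol amendment. Visits, ultrasound and reinterventions are already recorded, and 45 per arm still fits. The trade-off is that the 3- or 6-month result alone can no longer carry a confirmatory claim. Only six patients were enrolled when the article was written. Because follow-up assessors are not blinded, the amendment should be dated and made without reference to results by arm.
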